## Abstract

**Background:**

This trial aims at testing the efficacy of weekly reminder and motivational text messages, compared to usual care in improving adherence to Highly Active Antiretroviral Treatment in patients attending a clinic in Yaoundé, Cameroon.

**Discussion:**

This trial investigates the potential of SMS motivational reminders to improve adherence to Highly Active Antiretroviral Treatment in Cameroon. The intervention targets non-adherence due to forgetfulness and other forms of non-adherence.

**Trial Registration:**

Pan-African Clinical Trials Registry PACTR201011000261458

**
http://clinicaltrials.gov/
****NCT01247181**

## Background

Mobile text messages using the short message service (SMS) are a cheap and non-invasive means of communication that can be used to convey health related messages to owners of mobile phones. There is contradictory evidence concerning the role of mobile phones in ameliorating health outcomes, especially in less developed countries where private ownership and use of mobile phones is not as widespread as in other more developed countries[1]. Currently, Africa has the greatest uptake of mobile phone technology [2].

The advent of Highly Active Antiretroviral Therapy (HAART) has markedly reduced morbidity and mortality associated with the Human Immune deficiency Virus (HIV) [3]. Much effort has been put into the scaling up of access to HAART [4]. The efficacy of HAART depends largely on compliance to treatment regimens. Poor adherence is associated with poor virological and immunological response. It is also responsible for the development of resistant strains [5]. Very high levels (> 95%) of adherence are necessary for sustained clinical success [6].

Our search for papers on the use of SMS technology to improve adherence to HAART revealed two protocols for trials in Kenya (WelTel Kenya 1) [7] and India (HIVIND) [8]. The WelTel Kenya 1 trial reported significant improvements in adherence and viral load [9].

The World Health Organization (WHO) has prioritized the use of new technologies to assist health delivery in resource-limited settings [10]. The SMS is already used for business transactions, personal communication, advertising and betting. There is a potential for new benefits to be discovered in the use of mobile phone technology in health interventions for resource- limited countries [11]. In South Africa, the SMS has been demonstrated to improve HIV health care service delivery by ameliorating communication between health workers and patients, and also as an appointment reminder [12].

Additionally, a Cochrane systematic review found that mobile phone calls and reminders can improve adherence to tuberculosis care [13]. Another study investigating the use of mobile phone technology to improve adherence to HAART discouraged the use of phone calls as they are time and labor intensive [14]. A third study, investigating the use of text messaging to improve adherence to primary care found that it was more cost effective than phone calls[15]. The cost of phone calls may also be a hindrance in developing countries. The Indian trial [8] is testing automated phone calls coupled to picture messages. This may reduce the time and labor costs involved. Another study reported high satisfaction with two way text messaging [16]. These findings suggest that the more feasible application of the mobile phone in health would be the SMS.

The goal of this trial is to assess whether sending weekly motivational text messages via a mobile phone versus no text messaging will improve adherence to HAART and clinical outcomes among HIV positive patients over a 6 month period. We hypothesize that sending one weekly motivational reminder will produce a change in behavior to enhance drug or treatment adherence and hence clinical outcomes. SMS-delivered interventions are capable of producing a positive behavior change [17].

Participants will be selected from the Accredited Treatment Centre (ACT) of the Yaoundé Central Hospital (YCH).

## Methods and Design

The trial is registered with the Pan-African Clinical Trials Registry http://pactr.org as PACTR201011000261458 and with clinical trials.gov as NCT01247181.

### Study Design

Using a 1:1 allocation ratio, patients at the Yaoundé Central Hospital (YCH) Accredited Treatment Centre (ATC) will be randomized to either receive a text message reminder to take their medication or not (Figure 1: Consolidated Standards of Reporting Trials-CONSORT diagram of study design). Both groups of patients will benefit from the usual care provided in this centre which includes adherence counseling and rarely, home visits.

**Figure 1 F1:**
[figure not shown]
**Consolidated Standards of Reporting Trials-CONSORT diagram of study design**.

### Randomization

This is a parallel group design evaluating the effects of adding weekly SMS text messages using mobile phones to usual care (intervention) versus usual care alone (control) among HIV positive patients on HAART. Eligible and consenting patients will be randomized to intervention and control arms using 1:1 allocation ratio by opaque sealed envelope method. A computer generated randomization list will be generated using random block sizes of 2, 4 and 6, by the Father Sean O'Sullivan Research Centre Biostatistics Unit at St Joseph's Healthcare/McMaster University. The allocation codes will then be put in sequentially numbered opaque sealed envelopes and administered by the trained Research Staff at YCH ATC centre. Trained interviewers - blinded to group allocation - will collect data using a pretested data collection form containing socio-demographic data, clinical information and adherence rates at baseline, 3 and 6 months. The data analyst will also be blinded to group allocation.

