### Participants: inclusion/exclusion criteria

We will include subjects who are aged above 21 years, own a mobile phone and can read text messages, and who have been on HAART for at least a month. Informed consent is a prerequisite for participating in the study, and will be provided orally and in writing.

We will exclude participants who have been on HAART for less than a month, are aged less than 21 years. Participants who have used HAART for at least one month are chosen so that we can calculate a baseline figure for adherence.

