### Sample size

The sample size calculation is based on the test of the null hypothesis that the rates of adherence to HAART in the two groups (intervention and control) are equal. The primary measure of effect is the rate of adherence to ART treatment as measured by using the VAS over 6 months. The criterion for significance (alpha) has been set at 0.05. The test is 2-tailed, which means that an effect in either direction will be interpreted. The sample size was calculated using the WINPEPI (PEPI- for-windows) version 9.5 software [26]. With the proposed sample size of 82 in each of the two groups (i.e. assuming a 1:1 allocation ratio), the study will have power of 80% to yield a statistically significant result using a chi-squared test (assuming an intention-to-treat principle for the analysis) of the relative risk at alpha = 0.05. This computation assumes an adherence rate of 80% (for the intervention group) versus 60% (for the control group) at 6 months. These estimates are reflective of estimates from similar studies investigating SMS effect on drug adherences [27] and were modified to account for the type of intervention and patients for this study. We adjusted the sample size for a potential attrition rate of 20% (due to drop-outs) based on attrition rates to care in this centre. Therefore, the required sample size is 198 patients (99 per group). At the YCH ATC, on average, there are about 120 patients put on HAART per month. We estimate that about 90% will have mobile phones and would be eligible to participate in the study. Of these, it is expected that approximately 75% would be willing to participate in the study and will provide consent to participate in the trial. The expected period for recruitment will be one month to obtain 198 patients needed for the trial. It is feasible to recruit 198 patients in one month because we will also recruit from the large pool of old patients. Our study is designed to detect a 20% increase in adherence.

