### Analysis plan

The analysis and reporting of the results with follow the CONSORT guidelines [28]. The statistician/data analyst will be blinded to the study group. The process of patient selection and flow throughout the study will be summarized using a flow-diagram. The analysis results of patient demographics and baseline outcome variables (both primary and secondary) will be summarized using descriptive summary measures: expressed as mean (standard deviation) or median (minimum-maximum) for continuous variables and number (percent) for categorical variables. We will adopt an intention-to-treat principle to analyze all outcomes, meaning that data from participants will be analyzed according to the group to which they were randomized even if they do not receive the allocated intervention. We will also use multiple-imputation [29] to handle missing data. We will use the T-test for comparing groups on continuous outcomes and the chi-squared test for binary outcomes. All statistical tests will be performed using two-sided tests at the 0.05 level of significance. The Bonferroni method will be used to adjust the level of significance for testing for secondary outcomes to keep the overall level at alpha = 0.05. For all group comparisons, the results will be expressed as effect (or risk ratio for binary outcomes), corresponding two-sided 95% confidence intervals and associated p-values. P-values will be reported to three decimal places with values less than 0.001 reported as <0.001. Adjusted analyses using the following baseline covariates (age, gender, education, duration on HAART, HIV staging, nutritional status (BMI) and the presence or not of an opportunistic infection (OI)) will be performed using regression techniques to investigate the residual impact of key baseline characteristics on the outcomes. Goodness-of-fit will be assessed by examining the residuals for model assumptions and chi-squared test of goodness-of-fit. All analyses will be performed using SPSS (Statistical Package for the Social Sciences) version 16.0 for Windows.

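### Unadjusted T-tests on CD4 count, viral load, weight and BMI give up some precision in a sample of mixed HAART duration; name the duration-adjusted regression as the main analysis for these four outcomes

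*Protocol article*

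**What the plan says.** Under Participants, eligibility covers patients "who have been on HAART for at least a month", with no upper limit on treatment duration.

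Under Sample size, the recruitment forecast starts from new patients: "on average, there are about 120 patients put on HAART per month". Then "We estimate that about 90% will have mobile phones and would be eligible to participate in the study", and of these "it is expected that approximately 75% would be willing to participate in the study". The gap to the target is closed from a second source: "It is feasible to recruit 198 patients in one month because we will also recruit from the large pool of old patients". Neither source is given a number.

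Under Randomization, allocation is 1:1: "A computer generated randomization list will be generated using random block sizes of 2, 4 and 6". No stratification factor is named.

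Table 1 lists the T-test as the analysis method for change in weight, BMI, CD4 count and viral load, and the Analysis plan repeats the T-test for continuous outcomes. The Analysis plan then adds: "Adjusted analyses using the following baseline covariates (age, gender, education, duration on HAART" and further covariates, which it describes as key baseline characteristics. It does not say whether the unadjusted or the adjusted result is the one on which conclusions rest.

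**The concern.** How much CD4 count, viral load, weight and BMI change over six months plausibly depends on how recently treatment began. If the sample mixes recent starters with long-treated patients, the difference in mean change between them sits in the residual variance of every unadjusted T-test. An analysis that uses duration removes it.

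The protocol already treats duration on HAART as an important covariate and collects it, yet leaves it out of the tests that Table 1 assigns. At stake is precision on outcomes that are also tested at a Bonferroni-reduced level. There is a reporting issue too: with two analyses planned and neither named as the main one, the choice between them stays open if they disagree.

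**Working it through.** **1. The plan's own sample size.** Inputs from Sample size: 60% v 80%, two-sided alpha 0.05, power 80%.

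n per arm = [1.960 × √(2 × 0.7 × 0.3) + 0.842 × √(0.6 × 0.4 + 0.8 × 0.2)]² / 0.2² = 81.2, so 82. This reproduces the stated 82; power at 82 per arm is 80.4%. The calculation uses overall rates in each arm, so variation in adherence by HAART duration is already inside it.

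**2. The implied mix.** 120 × 0.90 × 0.75 = 81 recent starters; 198 − 81 = 117 others. Shares: 81/198 = 41% and 59%. This is a remainder calculation, not a stated recruitment plan.

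**3. A lower share for comparison.** If recruits mirrored the clinic (assumption), starters from the last six months would be 6 × 120 = 720 of the 6500 regular clients given under Trial Setting, or 11%.

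**4. Variance given up by the unadjusted T-test.** Let p be the share of recent starters and D the difference in mean change between recent and established patients, in within-group SDs. The protocol gives no value for D; 0.5 to 1 is an assumed range. Relative to an analysis that uses the grouping, variance rises by p(1 − p)D². The equivalent loss of sample is that rise divided by (1 + rise).

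| p | p(1 − p) | D = 0.5 | D = 0.75 | D = 1 |
|---|---|---|---|---|
| 41% | 0.242 | 6% | 14% | 24% |
| 20% | 0.160 | 4% | 9% | 16% |
| 11% | 0.099 | 2% | 6% | 10% |

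At 41% the equivalent loss of sample is 6%, 12% and 19%.

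**5. What that means for power.** Table 1 has nine secondary outcomes, so one reading of the Bonferroni rule is alpha = 0.05/9 (two-sided critical value 2.773). Suppose that the analysis using duration had 80% power. The unadjusted test then has power Φ[(2.773 + 0.842)/√(1 + rise) − 2.773]. At p = 41% this gives 77%, 73% and 68% for D = 0.5, 0.75 and 1. At p = 11% it gives 79%, 77% and 75%.

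**6. Chance imbalance.** With 81 recent starters allocated 99 v 99 without strata (hypergeometric), the number in one arm has SD 3.47. The between-arm difference in share has SD 2 × 3.47/99 = 7.0 percentage points and is 10 points or more in 15% of trials. For D = 0.5 to 1 this moves a mean difference by an SD of 0.035 to 0.07 within-group SD, against a standard error of √(2/99) = 0.14. It is the same variation as in step 4 seen from another side, not a second loss.

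**7. The primary outcome.** With an 81/117 mix, overall rates of 60% and 80%, and 82 per arm, using the grouping raises power from 80.4% to 80.8%, 82.2% or 84.6%. These correspond to assumed adherence gaps of 10, 20 or 30 points between recent and established patients.

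**The case against.** The strongest reply is that nothing here is an error. Blocked 1:1 randomisation without strata is sound in a single-centre trial of 198, chance imbalance under randomisation is not bias, and the unadjusted tests keep their error rate. All of that stands.

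A reader might infer that the trial will enrol 81 recent starters and 117 established patients. The protocol does not support this. It numbers neither source, and patients who start in the recruitment month are not eligible until they have completed a month on treatment, so the true mix is unknown. Nor does the 81, which is one month's starters, correspond to any particular cut such as six months. The size of D is likewise an assumption.

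A reader might also infer that imbalance threatens the comparisons generally, or adds to the loss of precision. It does neither. The unadjusted standard error already contains it, and the primary adherence comparison gains under two points of power for gaps up to 20 points.

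Finally, a reader might infer that the plan ignores duration. It does not: adjusted regressions that include duration are prespecified, and the protocol does not label them secondary.

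What remains is narrower. The argument that the variation is already in the stated 80% power holds only for the binary adherence outcome; no power calculation is given for the continuous outcomes. For those, Table 1 lists only the less precise test, and the adjusted analysis has no stated standing.

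**Conclusion.** The point holds as a low-cost improvement to the secondary analyses, not as a flaw in the randomisation or in the primary comparison. For change in CD4 count, viral load, weight and BMI, the tests assigned in Table 1 are valid but less precise than an analysis that the plan already contains.

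The size is 6% to 24% extra variance if 41% are recent starters, and about 2% to 10% if 11% are, in each case for an assumed difference in mean change of 0.5 to 1 SD. A smaller difference between recent and established patients would make the loss smaller still. That the sample will span short and long treatment follows from the eligibility criteria and the recruitment statement; its composition does not.

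**What to change.** In Table 1 and the Analysis plan, name the regression adjusted for duration on HAART as the main analysis for change in CD4 count, viral load, weight and BMI. Keep the unadjusted T-test as a supporting analysis. State in advance how duration enters the model (continuous, or grouped at a fixed cut), so that this is not chosen after the data are seen. The primary adherence analysis and the sample size need no change on this account.

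The cost is a few lines of text. Duration on HAART is already a planned covariate, so no new data are needed, and the regression is already planned. The change also settles beforehand which result counts if the two differ.

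Stratifying the envelopes by duration is optional. It would need a second numbered series at the one site and slightly more handling, and most of the precision is recovered by the adjustment alone.

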### Trial Setting

Cameroon is a sub-Saharan central African country, made of ten provinces and a population of 18 million inhabitants [18]. The Centre and capital province has a population of about 3.2 million inhabitants. The adult prevalence rate of HIV in the country is 5.1% [19]. Subjects will be recruited from the YCH ACT. This is an urban centre in the heart of the capital city, Yaoundé. The adult prevalence of HIV in the Centre province is 4.7%. The YCH is a tertiary level general teaching hospital with a capacity of 381 beds. It employs nearly 800 staff including 95 doctors and 270 nurses [20]. The ACT has a very high recruitment rate of approximately 40 new cases per week and caters for 6500 regular clients. It is the largest HIV clinic in the country and offers enormous potential for recruitment.

### Participants: inclusion/exclusion criteria

We will include subjects who are aged above 21 years, own a mobile phone and can read text messages, and who have been on HAART for at least a month. Informed consent is a prerequisite for participating in the study, and will be provided orally and in writing.

We will exclude participants who have been on HAART for less than a month, are aged less than 21 years. Participants who have used HAART for at least one month are chosen so that we can calculate a baseline figure for adherence.

### Intervention

We will send a short text message to the participants in the intervention group in both French and English. The content of the message will be motivating and will act both as a reminder and a cue to action (Figure 2: Example of a text message). The message will also contain a phone number they can call back if they need help. The content will be varied so as to retain participants' attention throughout the period of the study and to explore the various aspects of behavior change. The program secretary will have a list of phone numbers to which he/she will send the messages every week and will use the 'delivery report' function to ensure that the messages have been delivered. One message will be sent per week in the morning of a chosen day. The average cost for text messages on any networks is 50 CFA Frs. CFA (≈0.1 USD). Text messaging will be provided as an add-on to usual care which includes regular HAART counseling and occasional home visits.

**Figure 2 F2:**
[figure not shown]
**Example of a text message**.

### Control

In the control arm, patients will receive the usual care provided to all patients of the ATC which includes regular HAART counseling and occasional home visits. They will be given a number to call if they have questions. They will not receive any text messages, but they will be interviewed at baseline, 3 months and 6 months.

### Study Objectives

#### Primary Objective

The primary objective of this trial is to investigate the effect of adding the SMS to usual care versus usual care alone in improving and maintaining adherence to HAART in HIV positive patients on HAART at 3 and 6 months. There are several methods used to evaluate or measure adherence to medications, each with advantages and disadvantages [21,22]. Thus, there is no gold standard in measuring medication adherence [21,23]. The common approach is to use multiple methods to compare or assess the robustness of the estimates of adherence. For this study, we will use three commonly used measures of adherence - namely Visual Analogue Scale (VAS), Pharmacy Refill Data (PRD), and Self Report (SR). We will use VAS as the primary method of measuring adherence. The VAS is highly correlated with more objective methods like using Microelectronic Monitoring System (MEMS) caps [24]. VAS method has also been widely used in several RCTs evaluating different interventions including mobile text messaging to enhance adherence to HAART [8,21]. PRD and SR will be used to fill any missing data on VAS.

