### Outcome measures

Our primary outcome will be adherence rates, measured using VAS. SR and PRD will also be used to supplement VAS (Table 1).

**Table 1 T1:** Overview of outcome measures

Outcome measures	Scale	Type	Measure	Analysis method

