**Primary**				

Adherence at 6 months*				

VAS	Ordinal	Binary	VAS percentage >95%	Chi-squared test

Self report	Ordinal	Binary	% adherence in last month > 95%	Chi-squared test

PRD	Ordinal	Binary	% of complete refills >95%	Chi-squared test

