Adherence will be measured both as a continuous outcome (change in adherence) and as a binary outcome i.e. adherent (95% of pills taken) or non adherent (< 95% of pills taken). In literature, adherence data can be handled in a number of ways. The measures can be reported as the number of doses respected or can be combined into a composite score [21]. Even though combined measures are more correlated to clinical response, they are not very practical [22]. The data from the various adherence measures will not be merged. We will report the effects of the intervention on all the measures of adherence used, and compare them for discrepancies.

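### Missing values of the primary VAS endpoint are to be filled directly with refill or self-report data, which measure something else, and no order is set between this filling and multiple imputation

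*Protocol article*

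**What the plan says.** The Outcome measures section names the endpoint: "Our primary outcome will be adherence rates, measured using VAS". Table 1 gives each of three measures its own row, criterion and chi-squared test at 6 months. VAS is a percentage above 95%. SR is "adherence in last month > 95" per cent. PRD is the percentage "of complete refills >95" per cent.

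Three statements bear on a participant whose VAS is missing:

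- Primary Objective: "PRD and SR will be used to fill any missing data on VAS".
- Analysis plan, on missing data in general: "We will also use multiple-imputation [29] to handle missing data". No outcome is exempted.
- Analysis plan, closing paragraph on adherence: "The data from the various adherence measures will not be merged", followed by "We will report the effects of the intervention on all the measures of adherence used, and compare them for discrepancies".

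The Sample size section allows for 20% attrition, based on attrition from care at this centre, and randomizes 99 per group.

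**The concern.** A refill percentage or a self-reported percentage for the last month, entered in the VAS column, is a different measurement under the same name. The Primary Objective section itself says that no gold standard exists and that several methods are used to judge robustness. Copying one measure into another makes them agree by construction for the filled participants, which weakens the planned comparison for discrepancies.

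The fill sentence also leaves the handling of one value open. For a participant with no VAS but with a refill record, an analyst could copy the refill value, impute VAS from a model, or do the first for some participants and the second for the rest. The article does not say which comes first, whether PRD and SR enter the imputation model, or which of PRD and SR prevails when they disagree. At stake is the primary endpoint for up to about a fifth of participants.

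**Working it through.** **Inputs from the protocol (Sample size section).** Adherence 80% versus 60%, two-sided alpha 0.05, power 80%, 82 per group before attrition, 20% attrition, 99 per group randomized.

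**The plan's own figure.** The chi-squared formula with pooled variance under the null and no continuity correction is n = [1.960·√(2·0.7·0.3) + 0.842·√(0.8·0.2 + 0.6·0.4)]² / 0.20² = 81.2, rounded up to 82 per group. This reproduces the stated size. The 99 follows from 82 × 1.2 = 98.4, rounded up.

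**How many values are exposed.** 99 × 0.20 = 19.8, so about 20 per arm without a 6-month VAS and 79 with one.

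**Inputs assumed, because the documents give none.** The share classed as adherent among the 20 filled values per arm: 40%, 60% or 90% equally in both arms, or 90% versus 60%. All tests are uncorrected chi-squared.

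*Scenario 1, observed VAS 63/79 versus 47/79 (about 80% versus 60%)*

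| Handling | SMS | Control | Risk difference | RR | p |
|---|---|---|---|---|---|
| VAS only | 63/79 | 47/79 | 0.20 | 1.34 | 0.006 |
| Fill 40% both | 71/99 | 55/99 | 0.16 | 1.29 | 0.018 |
| Fill 60% both | 75/99 | 59/99 | 0.16 | 1.27 | 0.015 |
| Fill 90% both | 81/99 | 65/99 | 0.16 | 1.25 | 0.010 |
| Fill 90% vs 60% | 81/99 | 59/99 | 0.22 | 1.37 | <0.001 |

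*Scenario 2, observed VAS 59/79 versus 47/79 (about 75% versus 60%)*

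| Handling | SMS | Control | Risk difference | RR | p |
|---|---|---|---|---|---|
| VAS only | 59/79 | 47/79 | 0.15 | 1.26 | 0.042 |
| Fill 40% both | 67/99 | 55/99 | 0.12 | 1.22 | 0.080 |
| Fill 60% both | 71/99 | 59/99 | 0.12 | 1.20 | 0.073 |
| Fill 90% both | 77/99 | 65/99 | 0.12 | 1.18 | 0.058 |
| Fill 90% vs 60% | 77/99 | 59/99 | 0.18 | 1.31 | 0.006 |

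An equal fill adds the same count to both arms. The gap in counts stays at 16 (or 12) while the denominator rises from 79 to 99, hence 16/99 = 0.16 and 12/99 = 0.12. Multiple imputation under missing-at-random, without PRD or SR as predictors, would give about the VAS-only estimate. With them as predictors it would move some way towards the filled results.

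**The extreme case.** Suppose every missing VAS belongs to someone who left care, and the refill record scores that person as non-adherent. Then 0.80 × 0.80 = 64% and 0.60 × 0.80 = 48%, a difference of 16 points. Power at 99 per arm is Φ{[0.16·√99 − 1.960·√(2·0.56·0.44)] / √(0.64·0.36 + 0.48·0.52)} = 0.62, against the planned 0.80.

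**The case against.** A reader might infer that the protocol gives three mutually incompatible rules for missing VAS. The text does not go that far.

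- The sentence against merging follows a discussion of composite scores. It can be read as a rule against building a composite rather than as a missing-data rule. Read so, filling isolated gaps does not flatly breach it, although it still undercuts the comparison of measures promised in the next sentence.
- Multiple imputation is stated for all outcomes and introduced as an additional step. Filling where PRD or SR exists and imputing what remains is a possible joint reading. This makes the two statements an overlap without a stated order, not a contradiction.
- The Outcome measures sentence, "SR and PRD will also be used to supplement VAS (Table 1"), points to a table in which SR and PRD are separate rows. It most naturally means reporting alongside VAS, so the fill rule rests on the one sentence under Primary Objective.

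A reader might also infer that filling and imputation give opposite values for the same people. That needs every leaver to have a refill record scored as zero, which the documents do not say. Refill data could equally be missing for them, in which case imputation would apply either way. Imputation that uses PRD as a predictor would narrow the contrast further.

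The risk of choosing the rule by its result is limited, because the analyst is blinded to group and all three measures will be reported. At the design effect, p stays at or below 0.018 in the tabulated scenarios; it crosses 0.05 only at a smaller assumed effect.

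These points stand, and they reduce the strength of the claim. They do not remove it. The detail of an imputation model may be left to an analysis plan, but the protocol itself states a rule that puts other measurements into the primary endpoint.

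**Conclusion.** The concern holds in this form: direct filling of VAS from PRD or SR changes what the primary endpoint measures. It sits poorly with keeping the measures separate and comparing them, and its order relative to multiple imputation is not stated. If the planned 20% attrition occurs and every loss leaves VAS missing, about 20 of 99 values per arm are exposed.

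The effect on the result cannot be fixed from the documents. Under the assumed fill rates, the risk difference at an observed 80% versus 60% moves from 0.20 to between 0.16 and 0.22. At an observed 75% versus 60%, p moves from 0.042 to between 0.006 and 0.080. The figures of 64% versus 48%, with power of about 62%, are one extreme and not an expected outcome. The calculations show that the choice of rule can matter to the primary conclusion, not that it will.

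**What to change.** Replace the fill sentence under Primary Objective with a statement that missing VAS will be multiply imputed, with arm, baseline VAS, 3-month VAS, SR and PRD as predictors. Refill and self-report data then inform the missing values without standing in for them, and the general imputation statement in the Analysis plan applies to VAS with no competing rule. Keep VAS, SR and PRD as separately reported outcomes, as the Analysis plan already says.

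Under Outcome measures, at most clarify that supplementing VAS means reporting SR and PRD alongside it. A sensitivity analysis that counts participants who died or left care as non-adherent would be a useful option, but the correction does not depend on it.

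The cost is a few sentences, settled before the data are analysed, and one further analysis if the option is taken. All the predictors come from data that the trial already plans to collect.
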